## **1. Title and Phase of the Clinical Trial**

### **1.1. Title of the Clinical Trial**

Efficacy and safety of Galgeun-tang-ga-cheongung-sinyi for nasal congestion with common cold: a randomized, double-blind, placebo-controlled, parallel, multicenter clinical trial

(Protocol No. KIOM\_2024\_CC\_GGTCS)

### **1.2. Phase of the Clinical Trial**

Investigator-Initiated Trial

### 3. Background

Common cold is an upper respiratory tract infection syndrome caused by a mild virus. It occurs 2-4 times a year in adults and 6-8 times in children, causing personal distress and economic burden by leading to absenteeism from work and school. According to statistical data from the Health Insurance Review and Assessment Service, the total number of annual outpatient visits for common cold (J00) in 2023 was approximately 4.57 million, with total medical care benefit costs reaching about 174.9 billion Korean won. Common cold ranks 13th among the most frequent outpatient diagnoses in western medicine and 14th in Korean medicine.

Symptoms of the common cold vary, including rhinorrhea, nasal congestion, cough, headache, sore throat, myalgia, and fever, which interfere with daily life and reduce an individual's work capacity. While common cold is generally a self-limiting disease confined to the upper respiratory tract, it can occasionally spread to adjacent organs, causing other symptoms, or, rarely, lead to complications from bacterial infections. Although symptomatic treatment is typically employed for the common cold, some medications used in clinical practice have limitations. For example, first-generation antihistamines can cause severe drowsiness, and non-steroidal anti-inflammatory drugs (NSAIDs) can cause gastrointestinal issues, making long-term use difficult. Therefore, there is a need for safer and more effective treatments for the common cold, and Korean medicine treatments can be a viable option.

Rhinovirus is the most common viral cause of the common cold, accounting for 30-50% of cases. The most frequent symptoms are rhinorrhea, nasal congestion, and sneezing, with other symptoms including sore throat, headache, cough, and fever. Thus, prescriptions for nasal symptoms are frequently used in clinical practice. However, existing standard clinical practice guidelines for the common cold in Korean medicine have confirmed evidence for herbal treatments for symptoms such as cough, rhinorrhea, fever, and systemic pain, but lack sufficient evidence for nasal congestion. Therefore, there is a need to create new evidence in this area.

Galgeun-tang-ga-cheongung-sinyi (GGTCS) is an herbal formula composed of *Puerariae Radix*, *Ephedrae Herba*, *Cinnamomi Ramulus*, *Paeoniae Radix*, *Glycyrrhizae Radix et Rhizoma*, *Zingiberis Rhizoma*, *Zizyphi Fructus*, *Cnidii Rhizoma*, and *Magnoliae Flos*. It is a modification of the Galgeun-tang from the Shanghan Lun (Treatise on Cold Damage), with the addition of *Cnidii Rhizoma* and *Magnoliae Flos*. Galgeun-tang has been reported to activate immune cells, suppress allergic reactions, and possess anti-inflammatory, antipyretic, and analgesic effects. A study analyzing data from the Health Insurance Review and Assessment Service found that Galgeun-tang was the fourth most frequently used herbal insurance preparation prescribed to patients with allergic rhinitis. GGTCS adds *Cnidii Rhizoma*, which invigorates blood and Qi, dispels wind, and relieves pain, and *Magnoliae Flos*, which disperses wind-cold and unblocks the nasal passages, to the original formula. A preceding study reported an immediate therapeutic effect of GGTCS in patients with allergic nasal congestion as their main complaint. Thus, GGTCS is expected to be effective for common cold patients with nasal congestion as their primary symptom.

#### **4. Objectives**

To evaluate and compare the efficacy and safety of GGTCS compared with placebo for nasal congestion with common cold.

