| Efficacy Outcome Measures          | 
 
• Primary Outcome Measures 
 
1. Change in the WURSS-21-K total score (symptom score + quality of life score) from Baseline to Day 7
 
 
 
• Secondary Outcome Measures 
 
1. Change in the WURSS-21-K total score (symptom score + quality of life score) from Baseline to each time point (excluding Day 7)
 
2. Change in the WURSS-21-K symptom score from Baseline to each time point
 
3. Change in the WURSS-21-K quality of life score from Baseline to each time point
 
4. Change in the Nasal Congestion Severity Score from Baseline to each time point
 
5. Change in the Nasal Symptom Score VAS from Baseline to each time point
 
6. Change in the Systemic Symptom Score VAS from Baseline to each time point
 
 
 
 |

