#### 2) Rationale

This clinical trial is designed to evaluate the efficacy and safety of GGTCS for patients with nasal congestion due to the common cold. The primary outcome measure is the WRUSS-21-K. The change in the WRUSS-21-K from baseline to Day 7 (after a total of 21 doses, 3 times a day for 7 days) will be compared between the test group (GGTCS) and the control group (placebo).

The hypothesis for this clinical trial is as follows:

[Hypothesis]  $H_0$ (Null Hypothesis):  $\mu_t = \mu_c$  vs.  $H_1$ (Alternative Hypothesis):  $\mu_t \neq \mu_c$

$\mu_t$  : The mean change in the WRUSS-21-K score from baseline to Day 7 in the test group.

$\mu_c$  : The mean change in the WRUSS-21-K score from baseline to Day 7 in the control group.

Table 1. Change in WRUSS-21-K of Eungyo-san, Sams0-eum, placebo between pre- and post-treatment.

|                   | Pre-Treatment | Post-Treatment | Change (Before-After)* |
|-------------------|---------------|----------------|------------------------|
| Eungyo-san (n=44) | 56.28(30.47)  | 13.86(22.43)   | 44.00(22.27)           |
| Sams0-eum (n=42)  | 54.74(30.98)  | 17.05(24.29)   | 40.12(18.78)           |
| Placebo (n=42)    | 66.48(31.64)  | 33.33(30.02)   | 29.09(21.89)           |

\*: Change adjusting WRUSS-21-K score of baseline.

Previous studies (K.-I. Kim, M. Hong) showed that the mean (standard deviation) change in the WRUSS-21-K score from pre- to post-treatment was 29.09 (21.89) for the placebo group, 44.00 (22.27) for the Eungyo-san treatment group, and 40.12 (18.78) for the Samso-eum treatment group. The mean difference in effect was 14.91 for the Eungyo-san treatment group compared with the placebo group, with a pooled standard deviation of 22.09. The mean difference in effect for Samso-eum compared with the placebo group was 11.03, with a pooled standard deviation of 20.39. In this clinical trial, the significance level ( $\alpha$ ) was set at a two-sided 5%, and the power ( $1-\beta$ ) is 80%. Based on the results of the previous studies, the effect difference is set at 10 and the standard deviation at 21. The calculated number of subjects required to confirm the effect of the GGTCS group compared with the placebo group is as follows.

$$\left\{ \frac{2 \left( z_{1-\frac{\alpha}{2}} + z_{\beta} \right)^2 * \sigma^2}{|\mu_T - \mu_c|} \right\} = \left\{ \frac{2(1.96 + 0.84)^2 * 21^2}{10^2} \right\} = 69.227 \approx 70$$

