## 4) Assessments of WURSS-21-K, Nasal Symptom Score VAS, Systemic Symptom Score VAS, EQ-5D-5L

## 5) Assignment of Randomization Number

- Subjects who are deemed eligible for this clinical trial based on the inclusion/exclusion criteria will be assigned a randomization number in the following format, in the order of their enrollment.
- Site codes: Daejeon University Daejeon Korean Medicine Hospital 01, Kyung Hee University Korean Medicine Hospital 02, Pusan National University Korean Medicine Hospital 03

|                              |
|------------------------------|
| ✓ KIOM_2024_CC_GGTCS_0X_R000 |
|------------------------------|

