10.3.2. Secondary Outcome Measures

10.3.2.1.WURSS-21-K Symptom Score

- This score is calculated by summing the scores of the 10 questions in the WURSS-21-K that evaluate symptoms.
- Daily diary containing the WURSS-21-K will be distributed at Visit 2, and subjects will be instructed to complete it daily. It will be collected at Visit 3.

10.3.2.2.WURSS-21-K Quality of Life Score

- This score is calculated by summing the scores of the 9 questions in the WURSS-21-K that evaluate quality of life.
- Daily diary containing the WURSS-21-K will be distributed at Visit 2, and subjects will be instructed to complete it daily. It will be collected at Visit 3.

10.3.2.3.Nasal Congestion Severity Score

WURSS-21-K 상기도 감염 설문 - 21 일과 증상 기록

날짜(연월일):  
년 월 일

시간:  
오전 : 오후

병호:

다음 각각의 항목에 대하여 동그라미안에 체크하세요:

|                    | 아프지
않다
0        | 아주
조금
1         | 조금
2 3             | 보통
4 5             | 매우
6 7             |
|--------------------|-----------------------|-----------------------|-----------------------|-----------------------|-----------------------|
| 오늘 얼마나 아프다고 느끼십니까? |  |  |  |  |  |

각각의 증상에 대해 지난 24시간 동안의 감기증상으로 힘들었던 정도를 평가해주세요:

|               | 이러한 증상
은 없었습니다
0 | 아주
조금
1         | 조금
2 3             | 보통
4 5             | 매우
6 7             |
|---------------|------------------------|-----------------------|-----------------------|-----------------------|-----------------------|
| 콧물            |   |  |  |  |  |
| 코막힘           |   |  |  |  |  |
| 재채기           |   |  |  |  |  |
| 목이 아픔         |   |  |  |  |  |
| 목이 간질거리는 느낌   |   |  |  |  |  |
| 기침            |   |  |  |  |  |

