### **11.2.2. Secondary Outcome Measures**

- 1) The change from baseline to Day 7 in Nasal Congestion Severity Score, Nasal Symptom Score VAS, Systemic Symptom Score VAS, WURSS-21-K symptom and quality of life scores, EQ-5D-5L score, and duration of cold symptoms will be tested using the same method as the primary outcome measures.
- 2) To compare the differences in trend changes between groups, a Repeated Measures Analysis of Variance (RM ANOVA) will be used, with Dunnett's procedure for multiple comparison correction (comparing each time point to baseline).
- 3) The Global Evaluation of Efficacy satisfaction and cold recovery status on Day 7 will be analyzed using a Chi-square test. If the Global Evaluation of Efficacy score is treated as a continuous variable, an Independent t-test or Wilcoxon rank sum test will be performed.

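### The objective names efficacy for nasal congestion, but the only primary outcome scores the whole cold, so a significant primary result does not by itself show an effect on congestion

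*Protocol*

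**What the plan says.** **Target.** Section 4 states the objective as "To evaluate and compare the efficacy and safety of GGTCS compared with placebo for nasal congestion with common cold", in line with the title (section 1.1). Section 3 motivates the trial by saying that existing guidelines cover other cold symptoms "but lack sufficient evidence for nasal congestion". Section 8.1 lists nasal congestion first among the product's effects. Sections 5.3 (Rationale) and 6.2 put the aim differently: efficacy in patients whose nasal congestion is due to a cold. Section 5.1 makes a minimum congestion score an entry criterion.

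**Primary outcome.** There is one: "Change in the WURSS-21-K total score (symptom score + quality of life score) from Baseline to Day 7" (Synopsis; also section 11.2.1). The sample size is set on the same score: "the effect difference is set at 10 and the standard deviation at 21" (section 5.3).

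**Content of the score.** For the symptom part, section 10.3.2.1 says "This score is calculated by summing the scores of the 10 questions in the WURSS-21-K that evaluate symptoms". For the quality-of-life part, section 10.3.2.2 says "This score is calculated by summing the scores of the 9 questions in the WURSS-21-K that evaluate quality of life". Each of these items runs from 0 to 7 (section 10.3.1.1). The form reproduced in the protocol has one nasal congestion item among the ten symptoms.

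**Congestion itself.** The Nasal Congestion Severity Score (0 to 3) is one of ten secondary outcomes. Section 11.2.2 analyses "The change from baseline to Day 7 in Nasal Congestion Severity Score, Nasal Symptom Score VAS, Systemic Symptom Score VAS" and further measures in the same way as the primary.

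**Baseline for that score.** The Schedule Summary and the section 10.1 timetable both mark it at Visit 2. Item 4 of the Visit 2 procedures in section 10.2.2 reads "Assessments of WURSS-21-K, Nasal Symptom Score VAS, Systemic Symptom Score VAS, EQ-5D-5L" and leaves it out.

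**The concern.** The title, objective and background treat congestion as what the product should improve. The one confirmatory test is on a score made up mostly of other things: throat, cough, chest, fatigue and daily functioning. The protocol does not say why the total should stand for congestion.

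What is at stake is the conclusion. A significant total could come from items unrelated to the nose, yet the stated objective invites the reading that the product works on congestion. The measure that speaks to congestion directly is not tied to any conclusion, and its pre-treatment value is not secured by the visit procedures that sites follow.

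**Working it through.** **1. The plan's own figure.** Inputs from section 5.3: difference 10, SD 21, two-sided 5%, power 80%, 1:1 allocation, 20% dropout.

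- n per group = 2 × (1.960 + 0.842)² × 21² / 10² = 69.227 with unrounded normal quantiles, so 70.
- 70 / (1 − 0.20) = 87.5, so 88 per group and 176 in total.

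Both figures reproduce. The sample size arithmetic is not in question.

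**2. Weight of congestion in the primary score.**

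- Maximum of symptom plus quality-of-life score = 10 × 7 + 9 × 7 = 70 + 63 = 133.
- Congestion item: 7 / 133 = 5.3%.
- Crediting the breathing and sleep items in full as well: 21 / 133 = 15.8%.
- Section 10.3.1.1 instead sums all the questions. Its twenty 0-7 items alone reach 140, giving 7 / 140 = 5.0%, so the conclusion does not depend on which definition is used.

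**3. What the primary test needs.** With 70 per group:

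- Standard error = 21 × √(2/70) = 3.55.
- Smallest significant difference = 1.96 × 3.55 = 6.96 points.

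**4. Illustration: an effect on the congestion item alone.** This is an assumption for illustration and is not the protocol's hypothesis. Power ≈ Φ(difference / standard error − 1.96), ignoring the small opposite tail:

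| True difference in total | 70 per group | 88 per group |
|---|---|---|
| 2 points | 8.1% | 9.2% |
| 3 points | 13.2% | 15.6% |
| 7 points (item maximum) | 50.5% | 59.9% |
| 10 points (planned) | 80.4% | 88.5% |

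For 7 points at 70 per group, power runs from 60% to 46% as the SD goes from 18.78 to 22.27, the smallest and largest SDs of change in Table 1 of section 5.3. If the congestion, breathing and sleep items each moved by 2 points (assumed), the difference would be 6 points: 6 / 3.55 = 1.69, and Φ(1.69 − 1.96) is about 39%.

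**5. The baseline of the Nasal Congestion Severity Score, place by place.**

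- Schedule Summary and section 10.1: marked at Visits 1, 2 and 3, and daily.
- Section 10.2.1, item 10: assessed at Visit 1.
- Section 10.2.2, item 4 (Visit 2): not listed.
- Section 10.2.2, item 7: in the diary handed out at Visit 2 for daily completion. No entry before the first dose is required.
- Section 10.2.3, item 4 (Visit 3): listed.
- Section 9.4: dosing starts on the evening of the prescription date.

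The Visit 2 list contradicts both timetables. No visit procedure guarantees a Day 0 value before the first dose.

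**The case against.** The best defence is that congestion defines the population. Sections 5.3 and 6.2 speak of patients with nasal congestion, section 5.1 selects on it, and section 3 expects benefit in patients for whom it is the main symptom. On that reading, a validated whole-cold score with earlier trial data for sizing is a coherent primary outcome. This stands as a possible reading, and it is why the primary need not change. It does not remove the disagreement with the title, section 4 and the evidence gap named in section 3.

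A reader might infer from the table above that the trial is badly underpowered for a decongestant effect. The documents do not support that. The low figures hold only if nothing but the congestion item moves. The form asks about breathing, sleep and daily activities, and the protocol's own scale (section 10.3.2.3) defines severe congestion partly by interference with daily life or sleep. Section 3 also reports anti-inflammatory, antipyretic and analgesic effects of the parent formula. So 7 points is the direct contribution of one item and no ceiling on what relief of congestion could do to the total. A 7-point gap on the item would also need almost no placebo improvement on it, whereas Table 1 of section 5.3 shows placebo patients improving by 29.09 points on the total.

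The ranking of secondary outcomes is commonly left to a statistical analysis plan, which is not at hand, so its absence here is not a fault.

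A reader might also infer that sites hold only the screening score as baseline. That goes too far: the timetables and the diary both point to a Day 0 record, and screening is at most one day before Visit 2. What remains is an omission from one list, with no stated requirement that the score be taken before dosing.

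**Conclusion.** The point holds as a mismatch between the stated objective and what the primary test can show. Congestion contributes directly 5.3% of the primary score's range, or 15.8% if the breathing and sleep items are credited in full. A significant primary result supports an effect on overall cold severity in congested patients. It does not by itself support efficacy on congestion.

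It would be too strong to say that the primary result fails to answer the trial's question altogether: under the wording of sections 5.3 and 6.2 it does answer it. The power figures for a nose-only effect illustrate an assumption that the protocol does not make, and the verdict does not rest on them. The omission at Visit 2 is a small, separate contradiction, but it affects the baseline of the one outcome that measures congestion specifically. Should-fix.

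**What to change.** Keep the primary outcome and the sample size.

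1. **Reconcile sections 1.1 and 4 with sections 5.3 and 6.2, in one of two ways.**
   - Restate the title and objective as overall cold severity in patients with nasal congestion.
   - Or keep congestion as the target, name the Day 7 change in Nasal Congestion Severity Score as the single key secondary outcome in sections 10.3.2 and 11.2.2, and state that efficacy on congestion is concluded only if this is significant in addition to the primary. Otherwise the conclusion is limited to overall cold severity.
2. **Add the Nasal Congestion Severity Score to item 4 of section 10.2.2**, taken before the first dose, as both timetables already show, and use that value as the baseline for its change score.

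The cost is protocol wording, settled before unblinding. No patients are added, and the only measurement concerned is already in the timetables. Under the second option the congestion claim depends on a second test, and the protocol gives no effect size or SD for the 0-3 score, so the power of that test cannot be stated. That option limits over-claiming. It does not rescue an effect confined to the nose when the primary fails: with the 2 to 3 points assumed above, the primary would be significant in only about 8% to 13% of trials at 70 per group.

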## 5. Participants

### 5.1. Inclusion Criteria

- 1) Men and women aged between 19 and 75 years
- 2) Diagnosed with the common cold, symptoms occurring within 72 hours of the start of the trial
- 3) More than two symptoms related to the common cold including runny nose, nasal congestion, sneezing, sore throat, cough, headache, chills, and body aches
- 4) Nasal congestion severity score greater than 2
- 5) Those who voluntarily decide to participate in this clinical trial and give written informed consent to abide by the precautions after listening a detailed explanation of this clinical trial and fully understanding it.

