| Statistical Analysis    | 
• General Principles of Statistical Analysis
 
 
1. Definition of Analysis Sets 
For the analysis of data from this clinical trial, efficacy analysis will primarily use the Full Analysis Set (FAS) as the main method, and the Per Protocol Set (PPS) analysis will be used as a supplementary confirmation when necessary.
 
 
1) The FAS is defined according to ITT principle, which includes all randomized subjects who received at least one dose of the investigational product and have at least one post-baseline efficacy measurement. All data obtained from these subjects will be included in the analysis. However, subjects who do not meet a pre-established criteria will be excluded. The exclusion criteria for the FAS are as follows: 
 
i. Subjects who violate the inclusion or exclusion criteria
 
ii. Subjects who did not take the investigational product even once
 
iii. Subjects who did not provide any data after screening
 
 
 
2) The PPS analysis set consists of a subset of subjects from the FAS who have a drug compliance rate of at least 70% of the total investigational product dose, completed the entire trial process as specified in the protocol, and have no major protocol violations that could affect the results. The definition of major violations is based on the content described in section 7.1 of this protocol.
 
 
For the safety analysis of the data obtained from this clinical trial, all data from subjects who received at least one dose of the investigational product after randomization and underwent a safety evaluation will be included in the analysis. For safety analysis, subjects will be analyzed in the group they actually received treatment in.
 
 
 |

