## **7. Dropout and Early Termination Criteria**

### **7.1. Dropout**

Dropout refers to the premature termination of a subject's participation before completing all study procedures. The investigator may stop the treatment and observation and withdraw the subject, and the subject may voluntarily withdraw from the study at any time. A subject who meets any of the following criteria may be withdrawn from the study at the discretion of the principal investigator or responsible investigator. In the event of any of the following, the administration of the study drug and the trial itself may be discontinued, leading to withdrawal.

- 1) If a subject is confirmed to violate the inclusion/exclusion criteria after screening.
- 2) If a systemic disease, not discovered during pre-administration screening, is found in the subject.

- 3) If the investigator determines that continuous administration is inappropriate due to a serious adverse event in the subject.
- 4) If the investigator determines that continuous administration is inappropriate due to the severity of an adverse event.
  - Subjects who discontinue early due to an adverse event may receive appropriate treatment for the event if necessary.
- 5) If the investigator determines that the subject's symptoms have worsened and other treatment is required.
- 6) If the subject or their legal representative withdraws consent for participation in the clinical trial or requests to stop the administration of the investigational product (due to unsatisfactory therapeutic effect during the trial period).
- 7) If the subject's visits and follow-up are not possible.
- 8) If the subject violates the clinical trial protocol or leaves the hospital without permission, making it difficult to continue the trial.
- 9) If the subject takes any prescribed medication or over-the-counter medication that could affect the study's outcome (e.g., safety, pharmacokinetic properties) without the supervising physician's instruction during the clinical trial period (all periods after screening).
- 10) If the subject's medication compliance is significantly low, at less than 70%.
- 11) Other cases where the investigator judges the continuation of the clinical trial to be inappropriate.

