#### 10) Nasal Congestion Severity Score

- This is a 0-3 point scale used to assess the severity of nasal congestion symptoms, which subjects will self-evaluate (0=none, 1=mild, 2=moderate, 3=severe).
- It will be assessed at Visit 1.

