|-----------------------|-----------------------|-----------------------|-----------------------|-----------------------|-----------------------|-----------------------|
|  |  |  |  |  |  |  |

- This is a 0-3 point scale for evaluating the severity of nasal congestion symptoms. A score of 0 means no symptoms, while a score of 3 indicates severe symptoms that are difficult to endure and interfere with daily life or sleep.
- To be eligible for this study, subjects must have a nasal congestion symptom score of 2 or higher at screening.
- Daily diary containing the nasal congestion symptom score will be distributed at Visit 2, and subjects will be instructed to self-evaluate daily. It will be collected at Visit 3.

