## **11. Data Analysis and Statistical Analysis**

### **11.1. General Principles of Statistical Analysis**

#### **11.1.1. Definition of Analysis Sets**

The efficacy analysis of this clinical trial will primarily use the Full Analysis Set (FAS), with the Per-Protocol Set (PPS) used for supplementary verification as needed.

- 1) FAS: Adhering to the Intention-To-Treat (ITT) principle, the FAS includes all randomized subjects who have taken the investigational product at least once and for whom efficacy data have been collected at least once. Data from subjects not meeting pre-established criteria will be excluded. The exclusion criteria for the FAS analysis are as follows:
  - Violation of inclusion or exclusion criteria
  - Subjects who did not take the investigational product even once
  - Subjects who did not provide any data after screening
- 2) PPS: The PPS consists of subjects from the FAS who have a medication compliance of 70% or more, have completed all procedures as specified in the protocol, and have no major protocol violations that could affect the results. The definition of major violations follows the details in Section 7.1 of this protocol.

The safety analysis will include data from all subjects who have taken the investigational product at least once after randomization and for whom a safety assessment was performed. The analysis will be conducted based on the group to which subjects were actually assigned.

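### Sections 5.1 and 10.3.2.3 set different nasal congestion entry thresholds, so it is not fixed whether patients with a score of 2 belong in the trial

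*Protocol*

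**What the plan says.** Three parts of the protocol bear on this point.

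- **Entry threshold.** Section 5.1, item 4, lists as an inclusion criterion: "Nasal congestion severity score greater than 2". Section 10.3.2.3, which describes the same score as a secondary outcome, states: "To be eligible for this study, subjects must have a nasal congestion symptom score of 2 or higher at screening".
- **Scale.** Section 10.2.1, item 10, defines the self-rated score with four levels ("0=none, 1=mild, 2=moderate, 3=severe"). The criteria table under 10.3.2.3 describes the same four levels and no intermediate values.
- **Consequence of violating a criterion.** Section 11.1.1 makes the FAS the main efficacy set and lists among its exclusions "Violation of inclusion or exclusion criteria". The Synopsis has the same rule ("Subjects who violate the inclusion or exclusion criteria"). The PPS is a subset of the FAS, and its major violations are those of section 7.1, whose first item reads "If a subject is confirmed to violate the inclusion/exclusion criteria after screening". Section 7.1 leaves withdrawal of such a subject to the investigator's discretion and does not allow replacement.

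The inclusion list in the Synopsis cannot be read in the copy available, so it does not help either reading. Section 10.2.1, item 12, on confirming eligibility, does not repeat a threshold.

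**The concern.** Both sentences are written as the eligibility rule, for the same score, at the same visit. They give different answers for every patient who scores exactly 2. Three sites will recruit, and each could follow either sentence in good faith. Nasal congestion is the target condition in the trial's title and objective, so this criterion largely defines the patients to whom the result applies.

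The protocol also ties analysis-set membership to the inclusion criteria. The same score-2 subject is eligible under one section and a violator under another. The protocol does not say which section governs when the FAS is drawn up. At stake are the definition of the population, the number of subjects in the primary analysis, and a decision about that analysis set that the protocol ought to have settled.

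**Working it through.** **Step 1. The two rules on the scale.** The possible values are 0, 1, 2 and 3.

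| Source | Rule | Admitted scores | Population |
|---|---|---|---|
| 5.1, item 4 | > 2 | 3 | severe |
| 10.3.2.3 | ≥ 2 | 2, 3 | moderate and severe |

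The rules differ by exactly one category, score 2.

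**Step 2. What happens to a score-2 patient.**

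| Rule used to enrol | Rule used to judge violations | Outcome |
|---|---|---|
| 5.1 | 5.1 | not randomized; trial is severe-only |
| 10.3.2.3 | 10.3.2.3 | randomized and analysed |
| 10.3.2.3 | 5.1 | randomized, then removed from the FAS and so from the PPS |

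Only the third row loses randomized subjects from the efficacy analysis. The safety set in 11.1.1 has no eligibility exclusion, so these subjects would remain there.

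**Step 3. Reproduce the protocol's sample size.** The inputs from section 5.3 are two-sided alpha 5%, power 80%, difference 10, SD 21, 1:1 allocation and 20% dropout.

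n per arm = 2(z₀.₉₇₅ + z₀.₈₀)² × 21² / 10². With the rounded values 1.96 and 0.84 this is 2 × 7.84 × 441 / 100 = 69.1, which rounds up to 70. Allowing for dropout, 70 / 0.8 = 87.5, which rounds up to 88 per arm, 176 in total. Both figures match the protocol. The calculation does not depend on the congestion threshold.

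**Step 4. Size of the loss in the mixed case (illustration).** The share *s* of randomized patients scoring exactly 2 is not in the documents, and the values below are assumptions. Subjects left per arm are m = 88(1 − s), and by the normal approximation

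power = Φ(10 / (21√(2/m)) − 1.96).

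Worked example at s = 20%: m = 70.4; 21 × √(2/70.4) = 3.54; 10/3.54 = 2.825; 2.825 − 1.96 = 0.865; Φ(0.865) = 80.7%.

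| Assumed share s | Left of 88 per arm | Power | Left of 70 evaluable per arm | Power |
|---|---|---|---|---|
| 0% | 88.0 | 88.5% | 70.0 | 80.4% |
| 10% | 79.2 | 85.0% | 63.0 | 76.2% |
| 20% | 70.4 | 80.7% | 56.0 | 71.2% |
| 30% | 61.6 | 75.3% | 49.0 | 65.4% |
| 50% | 44.0 | 60.8% | 35.0 | 51.3% |

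The two-sample t calculation gives slightly lower values: 88.1% at 88 per arm, 79.9% at 70, 74.9% at 62 and 59.8% at 44.

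**Step 5. Break-even.** The 18 subjects per arm allowed for dropout (88 − 70) are used up when s = 18/88 = 20.5%, before any real dropout.

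**The case against.** The strongest reply is that the loss of subjects requires two incompatible readings at once. If 5.1 governs throughout, no score-2 patient is randomized and none can be removed. If 10.3.2.3 governs throughout, such patients are not violators. No section plans the mixed case, and one of the two sentences may be no more than a slip of wording. The power figures also rest on a share that the documents do not give. At 10% the power from 88 per arm is still 85%. All of this stands: the power table illustrates one scenario and is not a forecast.

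A reader might infer several stronger things that the documents do not support:

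- *That moderate patients will be deleted from the primary analysis.* This happens only in the third row of the table in Step 2.
- *That removing them biases the treatment comparison.* The screening score is recorded before randomization, so the removal by itself does not favour an arm. It costs power and narrows the population.
- *That a uniform screening score of 3 damages the primary model.* The ANCOVA in 11.2.1 adjusts for baseline WURSS-21-K total, not the congestion score. For the secondary congestion endpoint, the schedule shows a further assessment at Visit 2 (although the Visit 2 text in 10.2.2 omits it), so a constant baseline is not established.
- *That eligibility will be judged with results in view.* No section describes this, and sections 6.3 and 6.4 keep allocation undisclosed until the study ends, apart from emergencies.
- *That one of the two thresholds is evidently the intended one.* Nothing readable in the protocol shows which.

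None of this removes the contradiction. Section 5.1 is the formal list of criteria, 10.3.2.3 is explicitly worded as an eligibility condition, and no readable text reconciles them.

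**Conclusion.** The contradiction is certain and needs no assumption beyond the protocol's own scale. The two thresholds differ by the whole moderate category, so the trial population is not fixed as written. The link to the analysis is also in the text: a subject counted as an inclusion violator leaves the FAS and therefore the PPS.

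The numerical effect is conditional. It arises only where enrolment follows 10.3.2.3 and violations are judged by 5.1, and its size depends on an unknown share of score-2 patients. Under the assumed shares of 10% to 50%, power before dropout falls from about 88% to between about 85% and 60%. A share of about one fifth uses up the dropout allowance. The sample size calculation is not in error.

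The correction is still needed, because the criterion decides who is enrolled and can decide who is analysed.

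**What to change.** The sponsor should decide which threshold applies and state it in identical words in section 5.1, section 10.3.2.3, the Synopsis and the CRF eligibility check. Giving the admitted scores as a list would remove any doubt about the inequality. The choice between the thresholds belongs to the sponsor.

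The amendment should also state, before unblinding, that subjects enrolled in good faith under either wording before the correction are not excluded from the FAS on this criterion. The FAS exclusion in 11.1.1 and the Synopsis should then refer to the single reconciled criterion.

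The cost is a short protocol amendment and one CRF check.
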